#### **V.1.e. Expected adverse events – Definition of the benchmark document**

Are considered as expectable AE, any AE appearing in the benchmark document of the experimental MD. This MD does not own the CE mark. The benchmark is made of documents related to MFOCUS® experimental MD:

- First preclinical experimentations report with toric HIFU transducer, June 2009,
- MFOCUS® prototype handbook of EDP 800 548 A version, July,
- Liver metastases treated by HIFU - risks analysis – EDP 050 project, July 2009.

With all these elements, potential identified risks associated with HIFU treatment and therefore expectable AE are:

- For patients : contamination risk during probe setting,
- For patients : Burns of adjacent organs during HIFU shootings,
- For the medical team / user: injury risk resulting from a fall of the MD support (2 kg).

Besides during preclinical phase in animal, one peritonitis as a consequence of a biliary leak has been noticed. NB: The framework of this study does not include the treatment of this area.

## **V.2. Archiving of adverse events statements**

The original statements of AE done by investigators and checked by the Clinical Research Assistant (CRA) during monitoring visits to make sure that the elements of the clinical file are conform to what has been faxed to the Pharmacovigilance Centre.

AE statements and related documents are filed by the sponsor following predefined procedures.

A copy is kept by the investigator in the CRF.

## VI. STATISTICAL METHODS

### VI.1. Sample size and statistical rules

This study plans to include 32 to 38 patients:

#### VI.1.a. Phase I

**A group of 6 patients** will be included, in a sequential analysis divided into 2 steps following Lee's criteria (29). This analysis aims to stop prematurely the study if a failure rate  $> 15\%$  is observed.

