#### STATISTICAL RULES :

A failure is defined by at least one of the following situations:

- Overtime caused by shootings for 2 hurts exceeding 30 minutes,
- Impossibility to perform shootings on surface and/or in depth,
- Failing to respect requested asepsis procedures while setting the MD,
- Accidental hurt of nearby organs,
- Significant alteration of vital signs of at least  $10\%$  from its original value prior to the shootings.

[figure not shown]

To proceed to phase II will require to have fulfilled the following rule:

- 1st analysis after 2 patients:
  - If  $< 2$  failures are noticed  $\rightarrow$  continuation of the study and inclusion of 4 new patients,
  - If 2 failures the study is stopped.
- 2nd analysis after 6 patients:
  - If  $< 3$  failures are noticed  $\rightarrow$  continuation of the study and beginning of phase II (with Steering Committee's consent),
  - If  $\geq 3$  failures  $\rightarrow$  study is stopped.

NB: At the conclusion of the phase IIa, the Steering committee of the study will meet to examine all the brought together data, validate or not the criteria of continuation of the study and define more exactly the methodology of the phase IIb.

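### Phase I is said to stop at an observed failure rate above 15%, but its written rule continues at 1/2, 1/6 and 2/6 failures

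*Protocol*

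**What the plan says.** Section VI.1.a plans phase I as "A group of 6 patients", analysed in two steps by a cited sequential method (reference 29). It gives the purpose in one sentence: "This analysis aims to stop prematurely the study if a failure rate" above 15% is observed.

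The statistical rules that follow score each patient on a composite: "A failure is defined by at least one of the following situations". The situations are overtime above 30 minutes, inability to shoot at the surface or in depth, a breach of asepsis, injury to a nearby organ, and a change of at least 10% in a vital sign.

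The decision rule has two looks:
- After 2 patients: "If 2 failures the study is stopped". With 0 or 1 failure, 4 more patients are enrolled.
- After 6 patients: fewer than 3 failures leads to "continuation of the study and beginning of phase II", with the Steering Committee's consent. Three or more failures stop the study.

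For phase I the protocol gives no error level, no power, no unacceptable alternative rate and no stopping probability. By contrast, section VI.1.b gives detection probabilities for phase IIa, and alpha, power and both hypothesised rates for phase IIb.

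**The concern.** The purpose sentence and the decision rule describe the same gate but cannot both be true. With six patients the only observed rate at or below 15% is 0/6. Taken as written, the sentence would stop the study at the first failure, whereas the rule tolerates two. The two statements give opposite decisions at 1/2, 1/6 and 2/6, all of which are plausible results.

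Section II.2 describes a first evaluation in humans of a device without CE mark, and the composite includes organ injury and altered vital signs as well as feasibility items. Someone who relies on the 15% sentence would credit phase I with more protection than its numerical rule provides.

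**Working it through.** **Inputs.** From section VI.1.a: looks after 2 and 6 patients; stop at 2/2 or at 3 or more of 6; stated threshold 15%. Assumed: patients fail independently with a common probability p. The values of p other than 15% are illustrative, because the section names no other rate.

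**Step 1. Sentence and rule side by side.**

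| Failures | Observed rate | Sentence (observed above 15%) | Written rule |
|---|---|---|---|
| 0/2 | 0% | continue | continue |
| 1/2 | 50% | stop | continue |
| 2/2 | 100% | stop | stop |
| 0/6 | 0% | continue | continue |
| 1/6 | 16.7% | stop | continue |
| 2/6 | 33.3% | stop | continue |
| 3/6 or more | 50% or more | stop | stop |

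**Step 2. Where the boundaries could come from.** Exact binomial tails at p = 0.15:
- 2 patients: P(1 or more) = 27.75%; P(2) = 0.15² = 2.25%.
- 6 patients: P(2 or more) = 22.4%; P(3 or more) = 4.7%.

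So 2/2 and 3/6 are the smallest counts that reach a one-sided 5% level against 15% at their own look. Equivalently, the exact one-sided 95% lower limits are 22.4% for 2/2 and 15.3% for 3/6, but only 6.3% for 2/6. The boundaries are therefore reproduced, on a 5% level that the protocol does not state. The match holds per look; over both looks the chance of stopping at 15% is 5.9% (step 3).

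**Step 3. Stopping probability of the written rule.**

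P(stop) = p² + (1−p)² · P(Bin(4,p) ≥ 3) + 2p(1−p) · P(Bin(4,p) ≥ 2)

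- p = 0.15: 0.0225 + 0.7225 × 0.0120 + 0.255 × 0.1095 = 0.059
- p = 0.30: 0.09 + 0.49 × 0.0837 + 0.42 × 0.3483 = 0.277
- p = 0.40: 0.16 + 0.36 × 0.1792 + 0.48 × 0.5248 = 0.476
- p = 0.50: 0.25 + 0.25 × 0.3125 + 0.50 × 0.6875 = 0.672

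**Step 4. Stopping probability of the literal sentence.** One failure at either look exceeds 15%, so P(stop) = 1 − (1−p)⁶.

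| True failure rate | Written rule | Literal sentence |
|---|---|---|
| 5% | 0.4% | 26.5% |
| 15% | 5.9% | 62.3% |
| 30% | 27.7% | 88.2% |
| 40% | 47.6% | 95.3% |
| 50% | 67.2% | 98.4% |

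The written rule reaches a 50% chance of stopping at a true rate of about 41%, and 80% at about 58%.

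**Step 5. What a pass can show.** The worst passing result at the second look is 2/6. Its exact (Clopper-Pearson) one-sided 95% upper limit is 72.9%, about 73%.

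**The case against.** The strongest reply is that the operative rule is unambiguous and soundly built, so only one sentence is loosely worded. Much of this stands. Anyone running the trial can apply the rule as written, and step 2 shows no error in the boundaries. A reader might infer from the mismatch that the boundaries were miscalculated; the figures do not support that. Nor can one state as fact that the rule was designed to stop only on proof of a rate above 15%. That rests on an assumed one-sided 5% level, and the cited source is not at hand.

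A second reply is that the numerical rule is not the whole gate. Phase II also needs the Steering Committee's consent. Section II.3 has an independent committee decide each step and allows an early end for a serious event or accident. Section IV.5 allows termination for an unfavourable benefit/risk balance. This also stands: the probabilities above describe the rule alone. None of these safeguards carries a numerical criterion, however, so none resolves which threshold applies at 1/6 or 2/6.

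Third, low power comes with six patients, and section VI.3 already prescribes percentages with a 95% confidence interval. Both are true. The small sample is not the complaint, and no interval is missing. What remains is that the protocol attributes to the rule a threshold that the rule does not apply.

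**Conclusion.** The inconsistency holds: the stated threshold of an observed 15% is not what the written rule delivers, and the two disagree at 1/2, 1/6 and 2/6. At a true rate of 30%, twice the stated figure, the written rule alone stops 27.7% of the time and the literal sentence 88.2%. These values assume independent patients with a common failure rate, and the 30% is illustrative.

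Two stronger readings should be resisted. A reader might infer that the rule hardly ever stops a device failing in 30% of patients; 27.7% is more than one in four, and the figure should be quoted in place of an adverb. A reader might also infer that the protocol claims a pass establishes a rate of 15% or less. It makes no such claim. The caution about reporting in the proposed change is preventive.

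**What to change.** Reconcile the purpose sentence in section VI.1.a with the rule beneath it; the sponsor must say which is intended.

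- If the written boundaries stand, replace the sentence with a description of what they do: the study stops at 2/2 or at 3 or more of 6, and up to 2/6 observed failures continue subject to the Steering Committee's consent. State the error level intended and give the stopping probabilities over a range of true rates. Do not present a passed phase I as evidence that the failure rate is 15% or less.
- If an observed rate above 15% is really meant, the boundaries do not implement it and must be brought into line with the sentence.

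In the first case the cost is protocol wording and a less favourable account of the protection offered, with no change to sample size or conduct. In the second, the stopping rule itself changes, and the chance of stopping rises to the values in the right-hand column of the step 4 table.

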#### STATISTICAL RULES :

A failure is defined by at least one of the following situations:

- Overtime caused by shootings for 2 hurts exceeding 30 minutes,
- Impossibility to perform shootings on surface and/or in depth,
- Failing to respect requested asepsis procedures while setting the MD,
- Accidental hurt of nearby organs,
- Significant alteration of vital signs of at least  $10\%$  from its original value prior to the shootings.

[figure not shown]

To proceed to phase II will require to have fulfilled the following rule:

- 1st analysis after 2 patients:
  - If  $< 2$  failures are noticed  $\rightarrow$  continuation of the study and inclusion of 4 new patients,
  - If 2 failures the study is stopped.
- 2nd analysis after 6 patients:
  - If  $< 3$  failures are noticed  $\rightarrow$  continuation of the study and beginning of phase II (with Steering Committee's consent),
  - If  $\geq 3$  failures  $\rightarrow$  study is stopped.

NB: At the conclusion of the phase IIa, the Steering committee of the study will meet to examine all the brought together data, validate or not the criteria of continuation of the study and define more exactly the methodology of the phase IIb.

#### VI.1.b. Phase II

##### ✓ Phase IIa

**A group of 6 to 12 patients** will be included in 2 sequential steps with 3 to 6 patients in each. This number of selected patients has been defined by a classic dose escalation method used in clinical trials. The goal is to bring to light an insufficient accuracy of HIFU shootings if this event arises with a high frequency. Based on the binomial distribution, groups of respectively 3 and 6 patients allow a  $90\%$  probability to get at least one patient receiving an unacceptable shooting (inaccuracy), if this event occurs respectively in at least  $54\%$  and  $32\%$  of the cases.

[figure not shown]

• **1st step** (3 to 6 patients) :

A success is defined for one patient in a given amount of shootings ( $2 \leq n \leq 4$ ), if the mean distance between the closest hurt limit to the mark and the mark itself is  $< 5$  mm. Otherwise, the event will be considered as a failure.

3 patients will be included in the 1st step:

- If no failure is noticed → proceed to step 2;
- If 1 or 2 failure is(are) noticed 3 more patient are included in first step.
  - ↳ If  $> 2$  failures out of 6 → the study is stopped,
  - ↳ If  $\leq 2$  failures out of 6 patients → proceed to 2nd step
- If 3 failures are noticed → the study is stopped.

[figure not shown]

• **2nd Step** (3 to 6 patients) :

A success is defined for one patient in a given amount of shootings ( $2 \leq n \leq 4$ ), if the mean distance between the closest hurt limit to the vessel mark and the vessel it-self is  $\geq 5$  mm and  $< 10$  mm. Otherwise, the event will be considered as a failure.

3 patients will be included in the 1st step:

- If no failure is noticed → proceed to phase IIb;
- If 1 or 2 failure is(are) noticed, 3 more patient are included in first.
  - ↳ If  $> 2$  failures out of 6 → the study is stopped,
  - ↳ If  $\leq 2$  failures out of 6 patients → proceed to phase IIb,
- If 3 failures are noticed → the study is stopped.

NB: At the conclusion of the phase IIa, the Steering committee of the study will meet to examine all the brought together data, validate or not the criteria of continuation of the study and define more exactly the methodology of the phase IIb.

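### Phase IIa group sizes rest on a 90% chance of at least one inaccurate patient, which is not what the stopping rules act on; per step they stop with probability 71% at a 54% failure rate and 28% at 32%

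*Protocol*

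**What the plan says.** All of this stands in Protocol section VI.1.b, Phase IIa.

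- **Size.** Patients "will be included in 2 sequential steps with 3 to 6 patients in each".
- **Origin.** On where the size comes from, the section says: "This number of selected patients has been defined by a classic dose escalation method used in clinical trials".
- **Purpose.** On what the size is meant to achieve, it says: "The goal is to bring to light an insufficient accuracy of HIFU shootings if this event arises with a high frequency".
- **Quantitative support.** A binomial calculation for groups of 3 and of 6 yields 90% in each case. The event behind that figure is described as the "probability to get at least one patient receiving an unacceptable shooting (inaccuracy), if this event occurs respectively in at least" certain rates, namely 54% for the group of 3 and 32% for the group of 6.
- **Step 1 rules after three patients.** For a clean result the rule reads "If no failure is noticed → proceed to step 2". For a mixed result it reads "If 1 or 2 failure is(are) noticed 3 more patient are included in first step". When all three fail it reads "If 3 failures are noticed → the study is stopped".
- **Step 1 rules after six patients.** Three or more failures end the study; with two or fewer it goes on.
- **Step 2 rules.** The thresholds are the same, and passing leads to phase IIb.

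The section gives no probability of stopping for these rules.

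**The concern.** The stated goal is to reveal poor accuracy when it is common, and the 90% is the only number offered to show that the group sizes serve it. That number concerns seeing a single failing patient, and no single failure stops a step. One or two failures in three bring in three more patients, and a step with one or two failures in six still proceeds.

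Phase IIa is the counted accuracy gate before shots near important vessels (step 2) and before metastases are targeted (phase IIb). A sponsor, ethics committee or steering committee that takes the 90% as the sensitivity of this gate would overrate it, most of all at the 32% rate.

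**Working it through.** **Inputs**, all from Protocol VI.1.b, Phase IIa: 3 patients per step, expandable to 6; failure counted per patient; failure rates of 54% and 32%; the rules above. Let p be the true probability that a patient is a failure, with patients independent (the protocol's own binomial model).

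**1. The plan's own figure.** P(at least one failure in n) = 1 − (1 − p)^n.
- n = 3, p = 0.54: 1 − 0.46³ = 1 − 0.0973 = 0.903.
- n = 6, p = 0.32: 1 − 0.68⁶ = 1 − 0.0989 = 0.901.

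Both reproduce the stated 90%. The exact rates for 90% are 53.6% and 31.9%.

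**2. What these events mean under the rules.**
- At 3 patients, at least one failure means that the step does not pass straight through: it expands (1 or 2 failures) or stops (3 failures). The 90% at 54% is therefore the chance of not passing at once.
- At 6 patients, at least one failure separates no decisions. A step has 6 patients only if 1 or 2 of the first 3 failed, so a failure has already been seen. A step with no failure in 3 ends there. Viewed from its start, the chance that a step shows any failure at p = 0.32 is 1 − 0.68³ = 0.686.

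**3. Probability that a step stops the study.**

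P(stop) = p³ + P(1 of 3)·P(≥2 of next 3) + P(2 of 3)·P(≥1 of next 3)

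- p = 0.32: 0.0328 + 0.4439 × 0.2417 + 0.2089 × 0.6856 = 0.0328 + 0.1073 + 0.1432 = 0.283.
- p = 0.54: 0.1575 + 0.3428 × 0.5599 + 0.4024 × 0.9027 = 0.1575 + 0.1919 + 0.3632 = 0.713.

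A simulation of 200,000 runs per rate gave 0.283 and 0.712. Solving P(stop) = 0.90 gives p = 0.678.

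**4. Both steps.** Assuming the same p in each step and independence between steps, P(stop at either) = 1 − (1 − P(stop))².
- p = 0.32: 1 − 0.7167² = 0.486.
- p = 0.54: 1 − 0.2874² = 0.917.

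| True failure rate | Stop, per step | Stop at either step (same rate, independent) |
|---|---|---|
| 32% | 28.3% | 48.6% |
| 40% | 44.2% | 68.9% |
| 50% | 64.1% | 87.1% |
| 54% | 71.3% | 91.7% |

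**The case against.** **The protocol makes no false calculation.** The sentence names its event, at least one patient, and nowhere calls 90% a stopping probability; the rules follow directly below it. This stands. A reader might infer that the arithmetic is wrong, or that the protocol promises to stop with 90% certainty. The text supports neither.

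**One failure in three does have a consequence.** It blocks direct passage and forces three more patients. This stands too, so the 54% figure has a real meaning. It does not rescue the 32% figure.

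**The 6 might be the first three patients of both steps together.** At a common 32% rate, 90% would then be the chance that at least one step does not pass straight through. But the section sets 3 to 6 patients in each step, and the steps define failure differently: mean distance to a mark in step 1, a band of 5 mm to under 10 mm from a vessel in step 2. Even on this reading the figure is not a chance of stopping.

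**Over both steps the gate is stronger.** At 54% in each, the chance of stopping somewhere is 91.7%. This is fair and belongs beside the 48.6% at 32%. Both rest on a common rate that the differing definitions do not establish.

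**Counts are not the only safeguard.** Section II.3 gives decisions to proceed to an independent steering committee, and VI.1.b adds its review after phase IIa. Shots are confined to liver due for resection. A reader might infer that a device failing in 32% of patients would reach phase IIb about half the time (0.7167² = 51.4%), or that patients are left unprotected. The first holds only under the common-rate assumption and if the committee never intervenes; the second is not supported. The committee does, however, have no numerical criterion, so its effect cannot be counted.

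**A table of stopping probabilities could sit in a statistical analysis plan.** It could, and its absence alone would be no finding. The point is that the protocol itself states a property and fixes rules that do not have it.

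**Conclusion.** The point holds as a mismatch between the sample-size rationale and the decision rules. The 90% is correct for fixed groups of 3 and 6. For 3 patients it gives the chance of not passing straight through; for 6 it describes a group that the step rules never form from the start, and no decision depends on it.

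The probability of stopping per step is 28.3% at a 32% failure rate and 71.3% at 54%, and a failure rate of about 68% is needed for 90%. These per-step figures need only the protocol's binomial model and its rules as written. The two-step figures (48.6% and 91.7%) also assume equal failure rates and independence across steps, and all figures precede any committee judgement. The consequence is a misleading description of the accuracy gate in a small, mainly descriptive phase. It is worth correcting, but does not show that the phase is unsafe.

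**What to change.** In Protocol VI.1.b, Phase IIa:

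- Keep the 3-patient figure (90% at 54%), worded as the chance that a step does not pass straight through after its first three patients.
- Remove the 90% at 32% figure for 6 patients.
- State the stopping probabilities of the actual rules over a range of true failure rates, per step and for both steps, with the common-rate and independence assumptions given and a note that committee judgement comes on top.
- If the sponsor does intend a 90% detection property, the sentence and the rules must be reconciled; which of them gives way is the sponsor's decision.

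The cost is a text change, with no change to sample size or analysis unless the sponsor chooses to revisit the rules. The downside is that the stated figures become less favourable.

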### **I.2. Therapeutical use of ultrasounds**

HIFU are mechanical waves generated by an ultrasound transducer. A focused approach enables a sudden and accurate energy absorption in a distant but precisely defined targeted area. This induces a temperature increase going from 40 to 60°C in a few seconds and generates irreversible cell death through coagulative necrosis in an ellipsoidal shape with a 15 mm long axis and a diameter of 20 mm. There is no cooling effect of the perfusion because of the shortness of the phenomenon. The main asset of the technique is the use of non-ionizing waves which allows high focusing without hazardous effects on surrounding tissues. Plus it leads to almost no adverse effects. Thus, for about two decades, therapeutical ultrasounds implementations (hyperthermia, HIFU, lithotripsy) have been rising and explored in numerous ways: extracorporeal, percutaneous, transrectal, laparoscopic, transoesophageal, perioperative. Preclinical and clinical studies using these treatments concerned various pathologies such as glaucoma (10 ;11), localized prostate carcinoma (12 ;13), benign prostate hypertrophy (14;15), or other organs like bladder (16), breast (17), oesophagus (18), liver (19), uterine fibroma (20) or even brain (21). Because of the different ways to reach organs to be treated and depending on the way chosen for the treatment, many specific transducer technologies were developed. Nowadays, therapeutic ultrasounds appear as a great supplementary option to surgery among treatments using physical agents. Despite all these elements, HIFU technologies are to be improved concerning CLM treatment. It is in particular necessary to decrease the time of intervention because the elementary hurt HIFU is ellipsoidal and of small dimensions. A treatment by HIFU consists in juxtaposing in a precise way (generally by a movement automated by the probe of treatment) these elementary hurts until containing the tumor targeted with a margin of healthy tissues.

At the present time a treatment of prostate cancer by HIFU takes 149 minutes (22). Moreover, a real-time imaging device must be combined to HIFU to see precisely the treated area after each shooting.

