### I.3. Development of a toric hifu transducer for treatment of CLM

Cf. biblio (23;24)

[figure not shown]

Figure 1 : HIFU probe.

A perioperative ultrasound medical probe in treatment of CLM with HIFU has been developed and received at a preclinical phase in a porcine model. 7 cm^3 large (20 mm of diameter and 25 mm of long axis) unitary conical resections were done in 40 seconds with a crossed toric transducer which is an efficient result considering the time consumed and the volume treated. A hole in the middle of the medical device (MD) enables to add an echographic probe to localize and control liver metastases treatment. Characteristics of the generated hurts were studied on the models and in *in vitro* and *in vivo* preclinical studies.

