#### ✓ Primary objective

To estimate :

- **Accuracy of shootings** on a precise area (step 1) then on a zone to be spared (step 2),  
 ↳ THROUGH: both the distance between the hurt epicentre generated by hifu and a mark (step 1) and between the hurt limit and a vessel border previously marked (step 2). These sizes will be measured in mm during anatomopathological exam.

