#### **✓ Shootings process**

##### **⇒ Phase I**

The shootings will concern the healthy liver to remove, distant to the important vascular structures and metastases. Two HIFU shootings will be made on each patient:

- One hurt on the surface starting from the Glisson capsule and extending to subjacent hepatic parenchyma.
- One hurt at given depth, at least 10 mm deeper than the hurt done on the surface

NB: The shooting depth will be determined for each patient at the beginning of the operation, considering preoperative exams (scans, etc.), size and location of the liver part to be resected and physical structure of the patient.

⇒ **Phase IIa**

The shootings will concern healthy liver to be resected, distant (step 1) then close (step 2) to the important vascular structures of the liver. Several shootings HIFU will be made on each patient (ideally 4 hurts, minimum 2 hurts)

Step 1

Each mark will be spotted by a stationary mark set at a given depth (1st hurt on liver surface, 2nd hurt at depth of  $40 \pm 5$  mm, 3rd hurt at  $20 \pm 5$  mm, 4th hurt at  $60 \pm 5$  mm). Shootings will be performed by superimposing the theoretical hurt epicentre and the mark (the mark will have to be included in the generated hurt)

Step 2

Vascular structures will be colored in Patent Blue or Methylene Blue and will work as a mark. Shootings will be performed by positioning the closest theoretical hurt limits to a vessel at a distance of 5 to 10 mm from the vessel border.

⇒ **Phase IIb**

Shootings will concern small metastases ( $\leq 20$  mm) and peri lesional healthy liver. They will be juxtaposed on multiple plans in order to generate a large hurt containing the metastasis targeted and guaranteeing a sufficient safety margin in healthy liver. Several metastases can be treated in the same patient

✓ **Immediate following of the intervention**

The whole abdominal cavity will be explored to detect possible adverse effects, especially burns, involving adjacent organs to liver.

Once HIFU delivered the hepatectomy procedure will be totally identical to the one that would have been done if patient would not have received HIFU shootings.

The anatomopathological analysis will include, in addition, an analysis of each of the HIFU hurts.

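### The phase IIa step 2 success rule averages unsigned hurt-to-vessel distances and never requires the vessel to lie outside the hurt, so a shot that reaches or encloses the vessel can count towards success

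*Protocol*

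**What the plan says.** Protocol III.2.a gives the phase IIa primary objective as accuracy of shots on a precise area in step 1, "then on a zone to be spared (step 2"). The step 2 quantity is the distance "between the hurt limit and a vessel border previously marked (step 2"), and "These sizes will be measured in mm during anatomopathological exam". Neither the cutting plane nor a two- or three-dimensional reading is specified.

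VI.1.b (Phase IIa, 2nd step) turns this into the patient-level criterion. With 2 to 4 shots, the patient is a success "if the mean distance between the closest hurt limit to the vessel mark and the vessel it-self is" at least 5 mm and below 10 mm, and a failure otherwise. The count of failures among 3 or 6 patients decides whether phase IIb opens.

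IV.2.c (shootings process, Phase IIa) sets the aim for step 2 as "positioning the closest theoretical hurt limits to a vessel at a distance of 5 to 10 mm from the vessel border". For step 1 the same section adds a condition on position: "the mark will have to be included in the generated hurt". Phase IIb likewise requires the hurt to enclose the metastasis. Step 2 has no matching condition that the vessel be outside.

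Hurt size appears twice: I.3 describes a conical lesion, "20 mm of diameter and 25 mm of long axis", and I.2 describes HIFU lesions in general as "in an ellipsoidal shape with a 15 mm long axis and a diameter of 20 mm". No vessel diameter is given.

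**The concern.** The distance to a boundary is the same number on either side of it. In phase IIb a distance of 5 mm or more between target and hurt limit describes an enclosed object. In step 2 the same figure is meant to describe an untouched one, and the text does not say which side counts. Averaging over shots adds a second route: one shot that reaches the vessel can be offset by others.

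No other listed phase IIa criterion would reverse the score. The safety objective in III.2.a covers the opposite Glisson capsule, retro-peritoneal and retro-hepatic tissues and the diaphragm, not intrahepatic vessels. The assessment table in IV.3.c records the distance but has no item for a vessel touched or contained. At stake is a go/no-go decision on 3 to 6 patients in a first-in-human study, at the step meant to reveal inaccurate shots.

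**Working it through.** **The plan's own figure.** VI.1.b states that 3 and 6 patients give a 90% chance of at least one inaccurate patient if the true rate is at least 54% and 32%. From p = 1 - 0.10^(1/n): 1 - 0.1^(1/3) = 53.6% and 1 - 0.1^(1/6) = 31.9%. The figures reproduce, and nothing below changes them.

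**Sectional reading.** Suppose the pathologist measures on a cut across the vessel. For a vessel of diameter d (assumed) centred in the hurt, the border-to-limit distance is the inscribed radius of the hurt minus d/2.

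| Hurt shape | Inscribed radius | Distance by vessel diameter | Within 5 to <10 mm |
|---|---|---|---|
| Circular section, 20 mm (I.3) | 10 mm | d = 2, 4, 6, 8, 10: 9, 8, 7, 6, 5 mm; d = 12: 4 mm | d = 2 to 10 mm |
| Ellipsoid 15 x 20 mm (I.2) | 7.5 mm | d = 2, 4, 5, 6: 6.5, 5.5, 5.0, 4.5 mm | up to 5 mm |
| Cone 20 x 25 mm (I.3) | 10 x 25 / (10 + sqrt(10^2 + 25^2)) = 6.77 mm | d = 2, 3, 4: 5.77, 5.27, 4.77 mm | up to about 3.5 mm |

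The vessel must also be near the middle. In the 20 mm circle its centre may be off by at most 5 - d/2 mm: 4, 3 and 2 mm for d = 2, 4 and 6. That is 16%, 9% and 4% of the section area, from (5 - d/2)^2 / 100.

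**Three-dimensional reading.** A vessel that runs through the hurt crosses its limit, so the closest distance is 0 mm. The mean can hide this:
- two shots, 0 and 10 mm: mean 5.0, success;
- two shots, 0 and 12 mm: mean 6.0, success;
- three shots, 0, 7.5 and 7.5 mm: 15/3 = 5.0, success, with the other two at the midpoint of the planned window.

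**Size if a gross error is present in step 2.** Assumptions: sectional reading, 20 mm section, aim 7.5 mm, two shots, normal shot error, systematic error towards the vessel.

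| Vessel, SD | Scored as success at 15 / 18 / 20 mm error | Patients with vessel spared |
|---|---|---|
| 3 mm, SD 2 mm | 36% / 95% / 95% | 0% |
| 3 mm, SD 4 mm | 34% / 59% / 59% | 0% |
| 5 mm, SD 2 mm | 4% / 59% / 85% | 0% |

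With no systematic error and SD 2 mm, the written rule and a rule that fails any contact both give 92%. Errors of 10 mm or less hardly matter.

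**Would step 1 stop such an error first?** Take the VI.1.b step 1 rule as written (mean limit-to-mark distance below 5 mm), hurt radius 10 mm, two shots, the same constant error. With patient success probability s and f = 1 - s, the gate passes with probability s^3 + 3s^2 f (s^3 + 3s^2 f) + 3s f^2 s^3.
- 18 mm, SD 2: the mean distance centres on 18 - 10 = 8 mm with SD 2/sqrt(2) = 1.41, so s = P(Z < -2.12) = 1.7%; the gate passes in under 0.01%. At 20 mm, about 0%.
- SD 4: the gate passes in 0.5% (18 mm) and 0.01% (20 mm).
- 15 mm, SD 2: centred on 5 mm, s = 50%; the gate passes in 0.125 + 0.375 x 0.5 + 0.375 x 0.125 = 36%. At 36% patient success (3 mm vessel) step 2 then passes in 14%, so both pass in about 0.36 x 0.14 = 5%.

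Under the synopsis criterion for step 1 (epicentre within 5 mm of the mark), passage is about 0% for all three errors. Along the 25 mm axis the screen is weaker: at 18 mm the distance centres on 18 - 12.5 = 5.5 mm and the gate passes in 14% (SD 2); at 15 mm it passes almost always.

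**The case against.** The best defence is that the meaning is plain. The vessel is named as something to spare, and IV.2.c puts the near edge of the planned hurt 5 to 10 mm from the vessel border, the same window as the success rule. A pathologist who found the dyed vessel inside the necrosis would hardly report it as spared. Each hurt is analysed, hurt dimensions are measured blind by echography and pathology, pathology procedures are to be standardised in phase I, and the Steering Committee reviews all data before phase IIb. Step 1 would also nearly always stop a constant error of 18 to 20 mm.

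Much of this stands. A reader might infer that an enclosed vessel necessarily scores as spared. The documents do not support that: it needs a sectional measurement, or a vessel ending inside the hurt, and a suitable hurt shape and vessel size, none of which the protocol fixes. A reader might also take 36 to 95% as the expected rate of false successes. Those figures hold only for a gross error that arises after step 1 or passes it, and the protocol gives no evidence of one.

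What does not stand is that intent makes the rule complete. The inside/outside condition is written for step 1 and phase IIb and missing only where the vessel must be outside. The committee would receive a distance already scored as success. Under the three-dimensional reading, which removes the geometric problem, averaging can still absorb a contact.

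**Conclusion.** The point holds as a gap in a stated go/no-go definition. As written, a step 2 shot that reaches or encloses the vessel can count towards success under either way of measuring: through the missing sign on a section, or through the mean in three dimensions. The sectional route is limited to a nearly centred vessel of up to 10, 5 or about 3.5 mm, depending on hurt shape, with vessel diameter an assumption throughout. The averaging route needs no gross systematic error, only one contact offset by the other shots.

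The large false-success rates are conditional on a 15 to 20 mm error not caught by step 1. For a constant error across the 20 mm diameter, step 1 passes in about 0.5% or less at 18 to 20 mm and about 36% at 15 mm with SD 2 mm. The documents do not support the claim that the plan intends to count enclosed vessels as spared, or that misregistration would generally carry through to phase IIb.

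**What to change.** In VI.1.b (Phase IIa, 2nd step) and III.2.a, define the distance as signed: positive only when the whole vessel lies outside the hurt, zero or negative when the hurt reaches or contains it. Add that any shot whose hurt touches or contains the marked vessel makes the patient a failure, whatever the mean. Both parts are needed. A per-shot minimum on an unsigned distance would still accept an enclosed vessel on a section, and a signed mean alone would still let 0 and 10 mm average to 5 mm. Record contact or enclosure as a yes/no pathology item per shot, listed in IV.3.c.

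The cost is a short addition in two places and one form item, with no extra procedure. The sample size, the gate on failures among 3 or 6 patients and the 54% and 32% figures do not change. The downside is that the observed success rate can only stay the same or fall, probably slightly if targeting is sound.
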